## Abstract

**Background:**

Severe weight loss through means of bariatric surgery has been associated with loss of muscle mass due to lack of absorption of protein. The aim of this RCT is to investigate the effectiveness of protein supplementation in reducing the risk of developing protein malnutrition and muscle wasting in post-bariatric surgery patients in Qatar.

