Attempts to reverse obesity through weight loss have been the focus of the attention of many, including researchers, scientists and clinicians. This has been chiefly achieved via dietary and lifestyle modification, however, when these have not been successful, surgical options have been adopted for morbidly obese patients (ASMBS). Bariatric surgery (BS) has been shown to be the most effective type of approach to achieve and sustain significant weight loss in morbidly obese people [9]. BS is defined as a group of surgical procedures performed to facilitate substantial weight loss by reducing the size of the stomach and/or limiting absorption in the small intestine (American Society for Metabolic and Bariatric Surgery [1]. It is considered a highly efficacious treatment for extreme obesity. However, bariatric surgery patients frequently report difficulty initiating and maintaining healthy behavioral changes following surgery [4]. Most Post-bariatric surgery patients are strictly placed on liquid diet during the early post-operative phase and are practically unable to consume large quantities of food in one sitting or taking solid protein within the first months, which put them at a higher risk of developing protein malnutrition [8].

Post-surgery multivitamin and high protein supplementation is important to avoid any nutrient deficiency [3]. High protein supplements are mainly rich in protein and supplemented with vitamins and minerals. These supplements in general are inexpensive, widely distributed, and commonly used by people or patients who need nutritional supplementation while recovering from an illness or post-surgery especially post-bariatric surgery [3].

Protein supplementation is an effective approach to ensuring that post-bariatric surgery patients maintain muscle mass and healthy levels of the above-mentioned nutrients and body compositions [2]. In the absence of this, the weight loss achieved by the surgery may present a systematic issue leading to higher fat percentage and lack of these important elements that are essential for the function of the human physiology. The imbalance of such essential body compositions and nutrient can also lead to pathological and irreversible conditions. The objective of the present study is to examine the effectiveness of protein supplementation in reducing the risk of developing protein malnutrition that lead to low muscle mass and low protein level, in post-bariatric surgery patients.

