#### Secondary objectives

The percentage of weight reduction in the intervention in comparison with control groupThe difference in protein level (albumin/total protein) in post-bariatric patients receiving intervention compared with control groupThe blood level changes in Vit B12, Magnesium and Zinc in the intervention group in comparison with the control groupThe differences in the above changes in relation to types of bariatric surgery

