## Methods and design

This study is a double-blinded randomized control trial where both investigators and participants will be blinded to the treatment (intervention and placebo products are identical and unlabeled). The researchers will recruit participants early 2017. The randomization will be done on a weekly basis within blocks of 8 or 10 patients. This is roughly the number of patients available per week. A simple randomization process will be employed to assign patients to either groups- intervention & placebo. Using a computer generated random list, the treatment and the placebo will be allocated in a random manner to numbers that label individual patients. For the blinding, a dietician will assign the treatment and the control to patients as per the randomization results.

Both the intervention and control groups will receive standard dietary instructions in post-bariatric surgery period including hospital stay (1–2 days) and every month thereafter. The intervention group will receive protein supplement and the placebo group zero-protein supplement everyday over the study period (6 months). The placebo & the protein supplement slightly differ in the caloric content (the difference is 150 kcal/bottle). Although this difference is not clinically significant, particularly for the early post-operative phase, this issue will be addressed as a limitation for this study.

Investigators and researchers, including providers of care (rehab staff) in this study will be blinded to the intervention, i.e. they will not be aware of who is on protein supplement and who is on placebo. Patients will also be blinded to the intervention, i.e. they will not be aware whether they are taking protein or zero protein supplement. This dietitian is also responsible for filling the intervention & control ready-to-feed shakes into identical bottles labeled either A or B. The dietician will not have any other responsibility such as data entry or follow up of participants, as this will be done by the PI and research team. Un-blinding will be unlikely within the settings of our trial, however, any suspicion of un-blinding will be dealt with appropriately and may result into the cessation of participation in the trial.

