## Statistical analysis

Data analyses will be performed using the statistical software SPSS package 23. The main aim is to analyze Body composition and other anthropometric changes throughout the follow up. The normality of the variables will be assessed by the Kolmogorov-Smirnov test. Non-parametric tests will be used in case of non-normal distributions of variables. Characteristics and demographics of participants will be summarized, based on the assignment of treatment or placebo, using means and standard deviations (SD) for quantitative variables. Baseline data for the two groups will be compared using two tailed independent samples t-tests and the *P* value of this difference for each variable will be provided. During the follow-up, changes in weight, body fat percentage, muscle mass, total protein level, albumin level, vit B12, Zinc and Magnesium will be compared within groups using paired t-test and between groups using independent sample t-test. In the case of non-normal distribution of variables, any two independent (unpaired) samples Student’s t test will be replaced by Mann-Whitney U test. However, in the case of Two dependent (paired) samples Student’s t test, Wilcoxon signed rank (paired samples) test will be used. A multiple linear regression model will also be conducted to adjust for age and gender will be conducted. Other fundamental confounders such as diet intake are not incorporated into the multiple binary regression model. This is primarily because post-bariatric patients within the 1st few months (early post-operative phase) are both unable and not allowed to take any solid foods and few specific liquid foods such as milk and soups are recommended to them by the dietician. All patients are trained to follow such diet. Moreover, being an RCT, it is expected that all confounders (including hidden confounders) are balanced between the 2 groups and no assessment of baseline variables such as diet, physical activity and any other biological differences between the 2 groups is required. This is consistent with the CONSORT statement for RCTs.

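### The secondary objective on type of bariatric surgery has no matching analysis: the tests pool over procedures and the regression is fixed to age and gender

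*Protocol article*

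**What the plan says.** Under Secondary objectives, the protocol article lists comparisons of weight reduction, albumin and total protein, and vitamin B12, magnesium and zinc. It closes the list with the "differences in the above changes in relation to types of bariatric surgery".

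Under Statistical analysis, the changes "will be compared within groups using paired t-test and between groups using independent sample t-test", with rank tests as substitutes where a variable is not normally distributed. One model is added: "A multiple linear regression model will also be conducted to adjust for age and gender will be conducted". The section then defends this short covariate list. Diet is left out, and because the trial is randomised "it is expected that all confounders (including hidden confounders) are balanced between the 2 groups"; on that ground it says baseline diet, activity and other biological differences between the arms need no assessment.

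Under Methods and design, "A simple randomization process will be employed to assign patients to either groups- intervention & placebo", within weekly blocks of 8 or 10. No stratification by procedure is mentioned. Study participants and the eligibility criteria do not restrict the trial to one procedure.

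**The concern.** An objective that asks how changes differ by surgery type needs surgery type somewhere in the analysis. Here every named comparison is between or within the two allocated arms, and the only model has two named covariates. Followed literally, the plan reaches the end of the trial with one declared objective and no estimate for it. Any analysis by procedure would then be chosen after the data are in, most likely as separate subgroup t-tests.

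A second, smaller point follows from the article's own reasoning. The Abstract attributes to surgery a "loss of muscle mass due to lack of absorption of protein", and the Background says procedures may act by "limiting absorption in the small intestine", by reducing the stomach, or both. In a trial of an oral protein product, that makes procedure a plausible predictor of change. Leaving it out of a regression that is being fitted anyway gives up some precision.

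**Working it through.** **Setting the sections side by side**

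| Element | Surgery type included? |
|---|---|
| Secondary objectives, last item | Yes, it is the subject |
| Paired tests within arms | No |
| Independent-sample tests between arms | No |
| Regression | No; age and gender only |
| Randomisation | No stratification by procedure stated |

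The objective therefore has no counterpart in the analysis text. The article gives no figure on this point, so there is none to reproduce. The rest sizes the gain and the limits of a repair.

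**Inputs.** 80 per arm enrolled, 65 per arm evaluable and 90% power are from Sample size. The 5% type I error is taken as two-sided, which that section does not state. The 65 is used only as the number analysed; whether it follows from the article's own inputs is a separate matter. The share *f* of the less common procedure, the variance R² explained by surgery type and the difference δ between procedures are all assumptions.

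**Precision gain from the main effect.** The ratio of adjusted to unadjusted standard error is √(1 − R²). The power column starts from 90% unadjusted.

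| R² | Ratio | Reduction in SE | Power |
|---|---|---|---|
| 0.05 | √0.95 = 0.975 | about 3% | about 91% |
| 0.10 | √0.90 = 0.949 | about 5% | about 93% |
| 0.20 | √0.80 = 0.894 | about 11% | about 95% |

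**Chance imbalance is the same variance, not a further harm.** Take *f* = 0.3 and 80 per arm. The between-arm difference in that share has SD √(2 × 0.3 × 0.7/80) = 0.072. If the change differs by δ = 0.5 to 1 SD between procedures, the typical shift in the contrast is 0.072 × 0.5 = 0.036 SD to 0.072 × 1 = 0.072 SD. The unadjusted standard error is √(2/80) = 0.158 SD, a 95% half-width of 1.96 × 0.158 = 0.31 SD, and it already contains this. The implied R² is f(1 − f)δ² = 0.21 × 0.25 = 0.05 to 0.21 × 1 = 0.21, almost exactly the range in the table above. The SE reduction and the imbalance are two descriptions of one quantity.

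**What the interaction can deliver.** With 65 per arm, the main effect detectable at 90% power is (1.960 + 1.282) × √(2/65) = 0.57 SD. The interaction has SE = √[(4/130) × (1/f + 1/(1 − f))]. The supplement effect within the less common procedure has 95% half-width 1.96 × √(4/(130f)).

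| f | SE of interaction (SD) | Power if interaction = 0.57 SD | Interaction detectable at 80% power (SD) | Half-width in less common procedure (SD) |
|---|---|---|---|---|
| 0.5 | 0.35 | 37% | 0.98 | 0.49 |
| 0.3 | 0.38 | 32% | 1.07 | 0.63 |
| 0.2 | 0.44 | 25% | 1.23 | 0.77 |
| 0.1 | 0.58 | 16% | 1.64 | 1.09 |

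The term answers the objective with an estimate and an interval, not with a decisive test.

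**The case against.** The strongest objection is that a journal article condenses the plan, and that an interaction term for the fourth item in a secondary list is the sort of detail left to an analysis plan that is not shown. The analysis section never calls its list of tests exhaustive, and its remark about balance concerns the comparison of the two arms, not results by procedure. This stands in part: an unseen plan may contain the analysis, so it cannot be said that the trial will leave the objective unanswered. But the article is not merely silent. It names the covariates and argues that no others are needed, while its own objectives call for one more.

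A second objection is that the objective could be met by a descriptive summary of changes by procedure. That is a fair minimum reading. A summary pooled over arms would not, however, show whether the supplement-versus-control differences listed above it vary by procedure, and the model gives this at little extra cost.

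A third is that the benefit is small and rests on assumed inputs. This stands: if one procedure dominates, the precision gain largely disappears.

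Two stronger readings are tempting. A reader might infer that surgery type determines how much protein and B12 a patient absorbs. The Background offers only a general definition of bariatric surgery, the Abstract speaks of surgery as a whole, and no section links B12 absorption to procedure. A reader might also infer that omitting surgery type biases the supplement effect, or that chance imbalance is an additional harm. Randomisation keeps the unadjusted contrast valid, and the imbalance is already within its standard error.

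**Conclusion.** The point holds as a gap between a stated objective and the stated analysis, with a modest loss of precision beside it. As written, the article provides no estimate for its surgery-type objective. Adjusting for surgery type would lower the standard error by about 3% to 11% if it explains 5% to 20% of the variance; both that range and the procedure mix are assumptions. The primary comparison is not invalidated. The analysis that meets the objective would be weak, with about 16% to 37% power for an interaction as large as the detectable main effect over procedure splits from 10:90 to 50:50, and should be presented as exploratory. This is a worthwhile and cheap correction, not a fundamental flaw.

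**What to change.** In Statistical analysis, extend the regression and tie it to the objective, for instance: *The linear regression of change on allocated arm will adjust for age, gender and type of bariatric surgery. For the secondary objective on surgery type, a supplement-by-surgery-type term will be added, and the supplement effect with its 95% CI will be reported for each procedure from this model. This analysis is exploratory and has low power.* This should replace any separate subgroup t-tests. If the investigators do not want such an analysis, the objective should be withdrawn.

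With two or three procedures, the main effect costs one or two degrees of freedom and the interaction as many again. Intervals will be wide if one procedure is rare. No new measurement should be needed, but that procedure type is recorded is inferred from the objective itself; the article's measurement sections do not list it, so the investigators should confirm it.

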### Ethical consideration

Patients have the right to refuse participating in the study.Patients have the right to withdraw from the study at any time.All patients will be asked to provide consent to participate by signing the “patient consent form”, as an agreement to enter the study (Additional file 3).Researchers and other health-care professionals (investigators) will hold all information about the patients in strict confidence and disclose it only to those who have a legal right to this information. Moreover, patient visits will be conducted in private rooms.Any information that might lead to the identification of individual subjects will be omitted.De-identification of data and confidentiality of patients will be highly maintained throughout the trial“Intervene to protect patients” approach will be implemented if researchers are highly suspicious that a risk or abnormal lab value is imminent, and if necessary, staff will seek advice from more experienced professionals/clinicians.

Ethical approval was requested from both HMC and Qatar University IRB committees. Both committees granted the approval thereby confirming the legitimacy of our study. The RCT approval number from HMC is 16,433/16 (Additional files 4, 5).

### Trial registration

Our clinical trial was registered with ClinicalTrials.gov (US-NIH) PRS (protocol registration and results system), ID number: NCT03147453.
